### Outcomes

#### Primary outcome: Feasibility and acceptability.

Primary outcomes include feasibility and acceptability of the experimental intervention and are defined as:

A recruitment rate of ≥ 80% of the target sample in 9 monthsA retention rate of ≥ 80% to the study protocol of the recruited participants in the experimental group at cessation of therapy (eight sessions) ≥ 80% of the participants in the experimental group reporting a satisfaction rating of ≥ 7 on a Likert scale ranging from 1–10 with higher scores indicating a higher level of satisfaction with treatment

Feasibility will be evaluated at the end of the recruitment period (9 months) based on the proportion of the target sample enrolled. Retention and acceptability will be evaluated at treatment cessation and the post-treatment assessment (12 weeks post-baseline), defined as completion of the intervention (eight sessions) and completion of the 12-week assessment, and participant satisfaction measured post-treatment.

#### Secondary outcomes: Indications on treatment effect.

For secondary outcomes, the following measures are assessed at baseline and post treatment at 12 weeks follow-up:

Level of AVH is measured with the Psychotic Symptom Rating Scales, Auditory Hallucinations subscale (PSYRATS-AH) [54]. Outcome measures will include the PSYRATS-AH total score, as well as the two subscales: PSYRATS-AH-Frequency and PSYRATS-AH-Distress.Level of acceptance of an action in relation to hallucinated voices is measured with the self-report Voices Acceptance and Action Scale, specifically the VAAS-Action subscale [55].Level of assertive responding to voices is measured with the self-report Assertive Responding to Voices – the assertive subscale (Approve – Voices questionnaire) [56].Level of perceived power in relation to hallucinated voices is measured with the self-report Voice Power Differential Scale (VPDS) [57]. The total score will be reported as the main measure, and additionally, assertiveness and power items are separately reported.Beliefs about voices are measured with the self-report Revised Beliefs about Voices Questionnaires (BAVQ-R) including the Malevolence-, Benevolence- and Omnipotence subscales [58,59].

#### Exploratory outcomes.

Exploratory outcomes include:

Level of positive symptoms including AVH will be measured by the interviewer-rated Scale for the Assessment of Positive Symptoms (SAPS) [60]The interviewer-administered Brief Negative Symptoms Scale (BNSS) will measure level of negative symptoms [61].Self-reported level of negative symptoms is measured with the Self-evaluation of Negative Symptoms (SNS) [62].Ability to use emotion regulation strategies is measured with the self-report Emotion Regulation Questionnaire (ERQ) [63].Level of difficulties in emotion regulation is measured with the self-report Difficulties in Emotion Regulation Scale, short version (DERS-16) [64,65].The self-report Brief Core Schema Scales: Beliefs about self and others (BCSS) will measure core beliefs about self and others [66].Level of depressive symptoms is measured with the interviewer-administered Calgary Depression Scale for Schizophrenia (CDSS) [67].Level of suicidal thoughts is measured with the self-report Suicidal Ideation Attributes Scale (SIDAS) [68].Level of perceived childhood trauma experiences is measured with the retrospective self-report Childhood Trauma Questionnaire (CTQ) [69,70].Level of perceived self-efficacy is measured with the self-report General Self-Efficacy Scale (GSE) [71].Level of quality of life is measured with the self-report WHO well-being index (WHO-5) [72].Level of sleep quality and disturbances is measured with the self-report Pittsburgh Sleep Quality Index (PSQI) [73].Level of readiness for engaging in therapy is measured with the Readiness for Therapy Questionnaire (RTQ) [74].Level of insight into mental illness is measured with the self-report Birchwood Insight Scale (BIS) [75].Level of satisfaction with therapy is measured with the self-report Client Satisfaction Questionnaire (CSQ) [76].Level of symptoms of cybersickness is measured with the Simulator Sickness Questionnaire (SSQ) [77].The interviewer-administered Personal and Social Performance Scale (PSP) will measure daily life functioning [78].Level of social functioning is measured with the self-report Social Functioning Scale (SFS) [79].

#### Electroencephalogram examinations at baseline and post treatment.

EEG recordings will be conducted at baseline and post-treatment. Participants will complete five paradigms commonly used to assess auditory processing deficits in schizophrenia:

P50 sensory gating: Measures suppression of the P50 response to paired auditory clicks, reflecting sensory gating [80–82].Mismatch Negativity (MMN): Captures automatic detection of auditory deviations in frequency or duration, presented while participants watch a muted video to maintain attention [83,84].Selective Attention (SA): Assesses attentional control using a deviant-tone detection task, alternating between ears [85].40 Hz Auditory Steady-State Response (ASSR): Evaluates gamma-band oscillatory responses to 40 Hz click trains [44,86].Resting State: Measures spontaneous EEG activity with eyes open and gaze fixed [87]. These paradigms were selected based on previous studies showing consistent impairments in early auditory processing in schizophrenia that are thought to contribute to delusional beliefs, hallucinations and cognitive and negative symptoms [43–47].

These paradigms were selected due to their robust associations with schizophrenia-related impairments in sensory gating, auditory processing, attention, and oscillatory activity [43–47]. The P50, MMN, and ASSR paradigms have been linked to cognitive dysfunction and are considered promising biomarkers for treatment response [43,44,46,88–92]. Deficits in selective attention have also been reported in schizophrenia and are considered relevant to cognitive and functional impairments, with underlying disruptions in frontotemporal networks [42]. Resting-state measures provide additional insight into large-scale oscillatory abnormalities in psychosis [93,94].

EEG assessments will be used to explore potential neurophysiological mechanisms underlying therapeutic effects. The EEG component of the study has two aims:

1)To assess P50 sensory gating as the primary neurophysiological outcome. We hypothesize that both groups will show improved P50 suppression, with a potentially greater improvement in the biofeedback group. This hypothesis builds on previous findings suggesting a link between VR-assisted therapy and enhanced P50 suppression [49].2)To explore broader auditory and attentional processing using MMN, ASSR, SA, and resting-state paradigms. These measures will be analyzed exploratorily to identify possible treatment-related neural changes beyond sensory gating.

EEG measures may thus provide insight into neurophysiological adaptation associated with treatment effects and help clarify the potential added value of integrating biofeedback.

Recordings will use a 64-channel BioSemi ActiveTwo System (Amsterdam, Netherlands) with electrodes arranged per the extended 10–20 system and a 2048 Hz sampling rate. Participants will be seated in a sound-insulated cabin (40 dB), and auditory stimuli will be delivered binaurally via insert earphones (E-ARTONE 3A) using Presentation® software (Neurobehavioral Systems, Berkeley, CA). Preprocessing and analysis will follow standard pipelines, adapted for each paradigm.

#### Qualitative data.

Semi-structured individual interviews with participants in the experimental group will be conducted following completion of treatment, as well as an interview with the therapists delivering the intervention. The interviews will be conducted by a trained member of the research team who are not involved in other parts of the study and are not blinded to treatment allocation. The interviews will involve questions regarding:

Experiences with the biofeedback equipment, which involve the participants’ experience of wearing the device during therapy sessions, as well as their experience with the technical aspects.Experiences with the visibility of the feedback display in the VR environment.Experiences with receiving a direct measure of anxiety-related responses during therapy, which involve topics such as the role of biofeedback in supporting the therapeutic aims and sharing these physiological responses with the therapist.

Examples of questions used to guide the interviews include: “How did you experience wearing the biofeedback equipment during the therapy sessions?”, “How did you experience having a visible measure of your emotional responses during therapy?”, and “What role, if any, did the biofeedback play in helping you manage uncomfortable or distressing emotions during therapy?”.

### Randomization and blinding

A computerized randomization system in the Research Electronic Data Capture (REDCap) [95] is used to randomly allocate participants to the two interventions. To equalize participants in both arms, an external party has created and uploaded a block randomization list in REDCap. The block sizes are unknown to the assessors conducting the outcome evaluation and the therapists. The randomization is unstratified. Study therapists, who are not blinded to the intervention allocation, will be responsible for the randomization process. Assessors are blinded to intervention allocation until statistical analyses are completed. Participants will be instructed to conceal their treatment allocation from the assessors both at baseline assessment, and follow-up assessment.

### Apparatus

#### VR headset and software.

To enhance the participant’s experience of being immersed in the VR-environment, we will use an Oculus Quest 2 VR headset and noise-cancelling headphones. Audio-visual VR presentation software programs for both intervention groups were developed by HekaVR A/S (Copenhagen, Denmark).

#### PPG device used for anxiety monitoring.

The selection of the device for measuring physiological signals was based on criteria such as accuracy, reliability, ease of use and patient comfort. HR and HRV data are collected during therapy sessions using the Shimmer3 GSR+ Unit. This unit utilizes the non-invasive method photoplethysmography (PPG), an optical technique that estimates heart rate based on blood volume changes in the microvascular tissue [38], to obtain these measures. This is a biosensing technique is compatible with the VR setup and have previously been used to assess anxiety levels [38,96,97].

The device is programmed to calculate a real-time Stress Index designed to reflect sympathetic dominance. The index is based on the stress response pattern characterized by increased HR and decreased HRV, reflecting sympathetic dominance and parasympathetic withdrawal during acute stress [98–100]. The Stress Index is calculated as follows:

Stress Index = 1 + 9 × (0.6 × HR_stress + 0.4 × HRV_stress)^1.5

HR_stress = clip((HR – 40)/80, 0, 1)

HRV_stress = 1 – clip((lnRMSSD – 1)/5, 0, 1)

Where HR represents heart rate (expected range 40–120 bpm), lnRMSSD is the natural logarithm of the root mean square of successive differences (RMSSD), which is a time-domain measure of heart-rate variability, and clip(a, min, max) restricts a to the interval [min, max].

At the beginning of each session, a baseline measurement is recorded, and the biofeedback “thermometer” shows changes relative to this session-specific baseline. The Stress Index formula applies fixed normalization ranges for all participants, but the visual biofeedback shown in VR is recalibrated to each participant’s session-specific baseline. Higher scores indicate elevated physiological arousal, and the metric is continuously updated and displayed to both the therapist and the participant within the VR software.

In this feasibility trial, the Stress Index is used solely as a real-time feedback signal. Continuous raw biofeedback data are not stored, and the metric is therefore not analyzed as a standalone quantitative outcome. The Stress Index has not yet undergone formal psychometric validation, and its use in the present study is exploratory.

### Analyses

#### Statistical analysis.

The primary feasibility evaluation will be based on data collected at the final post-intervention assessment (12-week follow-up). The PSYRATS-AH total score is the primary clinical outcome.

Secondary clinical outcomes (e.g., symptom severity, functioning, and quality of life) will be analyzed using ANCOVA comparing groups at 12 weeks, with the corresponding baseline value included as a covariate. Potential baseline imbalances on other measures will be addressed in sensitivity analyses by additionally adjusting for the imbalanced baseline variables. Missing data will be handled using multiple imputation under a missing-at-random assumption (M = 100).

This feasibility trial is not powered to detect statistically significant between-group differences in secondary clinical outcomes. Accordingly, analyses of secondary outcomes will be considered exploratory and hypothesis-generating, and will be interpreted primarily in terms of estimated effect sizes and 95% confidence intervals rather than statistical significance. Bayesian analyses may be used for selected secondary outcomes to aid interpretation of non-significant findings. Given the small sample size and feasibility focus, no formal adjustment for multiple comparisons will be applied. Results will be interpreted cautiously and used to inform outcome selection and sample size calculations for a future definitive trial.

#### Analysis of EEG data.

The EEG data will be down-sampled and filtered for artifact removal. The exact parameters depend on the specific paradigm. Outcome measures before and after the intervention will be analyzed with repeated-measures analysis of variance. From the P50 paradigm, the response in temporal domains (S1 and S2 amplitude, and the P50 ratio: S2/S1) will be extracted [49]. From the MMN paradigm, the MMN and P3a component from the three different deviants will be extracted. Likewise, the N100, P200, P300, MMN, and PN (processing negativity) will be extracted from the SA paradigm. The 40 Hz ASSR will be analyzed using time-frequency decomposition and the power and inter trials phase coherence around 40 Hz will be extracted. Finally, the spectral power of five canonical frequency bands (delta, theta, alpha, beta, and gamma) will be extracted from the resting-state paradigm.

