## Materials and methods

### Study design

The study is carried out at the Mental Health Centre Copenhagen, Mental Health Services, Capital Region of Denmark. It is a two-arm pilot randomized clinical trial (RCT) that utilizes a mixed-methods design combining quantitative and qualitative methods. A total of 30 participants diagnosed with a schizophrenia spectrum disorder based on ICD-10 (codes: F20, 22–23, 25–29) from the psychiatric outpatient facilities in the Capital Region of Denmark and the Region Zealand will be enrolled. The participants will be randomly assigned to one of the two treatment arms:

Control group: 8 sessions of VR-assisted therapyExperimental group: 8 sessions of VR-assisted therapy augmented with real-time biofeedback

Participants will be assessed at baseline and at treatment cessation (12 weeks post baseline) (Fig 1). In addition to clinical evaluations, both time points will include EEG assessments to examine the intervention’s potential effects on brain activity.

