Despite demonstrated clinical benefits of VR-assisted therapy for auditory verbal hallucinations (AVH), the precise therapeutic mechanisms behind VR-assisted therapy remain unclear. Understanding these mechanisms is crucial for optimizing treatment protocols and tailoring interventions to individual patients [15,104]. Emerging evidence suggests that affect regulation may play a central role by helping patients manage the emotional distress associated with AVH [15,18,19]. However, systematic investigation of affect regulation as a core therapeutic mechanism within VR-based interventions for AVH is still lacking. The present study aims to contribute with new knowledge on whether and how affect regulation functions as a key underlying therapy process in VR-assisted treatments for AVH.

A further strength of the study is the integration of multiple data sources to evaluate both the treatment and study protocol. These exploratory measures are included to inform outcome prioritisation and protocol optimisation for a future definitive trial, rather than to support confirmatory hypothesis testing. Pre- and post-treatment EEG examinations will provide valuable insights into neural mechanisms underlying AVH, which will enhance the understanding of the subgroups of participants who respond differently to the treatment. Furthermore, if EEG markers such as P50 suppression show improvement post-treatment, this could suggest that the intervention modulates underlying sensory gating mechanisms associated with AVH. These findings would be in line with previous pilot work suggesting that improvements in P50 gating may reflect neural normalization in response to avatar-based interventions [49].

The added value of biofeedback will be evaluated based on convergence across clinical outcomes, qualitative feedback, and exploratory EEG markers, enabling pre- to post-intervention comparisons between the biofeedback and no-biofeedback groups. However, a key limitation is that raw biofeedback signals are not recorded during sessions, which restricts the ability to examine how physiological responses unfold in relation to therapeutic content. While this approach allows for preliminary insights, future studies should aim to capture raw biofeedback signals to enable a more detailed examination of biofeedback mechanisms and their therapeutic relevance.

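### Analysing the EEG outcomes, including P50, by pre/post repeated-measures ANOVA is valid but less precise than the baseline-adjusted ANCOVA already planned for the clinical outcomes

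*Protocol article*

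**What the plan says.** The Analysis of EEG data section sets one method for all EEG paradigms: "Outcome measures before and after the intervention will be analyzed with repeated-measures analysis of variance". The section on EEG examinations ranks one of them first ("To assess P50 sensory gating as the primary neurophysiological outcome") and gives its hypothesis: "We hypothesize that both groups will show improved P50 suppression, with a potentially greater improvement in the biofeedback group".

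The Statistical analysis section treats the secondary clinical outcomes differently. They are "analyzed using ANCOVA comparing groups at 12 weeks, with the corresponding baseline value included as a covariate". The design is the same for both sets of outcomes: two randomised arms, one baseline visit and one visit at 12 weeks (Study design). No reason is given for using a different model for EEG.

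On interpretation, the Discussion says that "if EEG markers such as P50 suppression show improvement post-treatment, this could suggest that the intervention modulates underlying sensory gating mechanisms". It also describes the data as "enabling pre- to post-intervention comparisons between the biofeedback and no-biofeedback groups".

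**The concern.** There are two separate issues.

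**Precision.** The only EEG contrast protected by randomisation is the difference between arms. With about 15 people per arm, the width of its confidence interval is most of what the analysis can deliver, and the Statistical analysis section says that secondary outcomes will be read mainly through effect sizes and 95% intervals. A model that takes the simple difference from baseline, rather than adjusting for baseline, gives a wider interval than the data already collected allow.

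**Interpretation.** The first half of the P50 hypothesis, improvement in both groups, is addressed by the time main effect. Both arms receive VR-assisted therapy and there is no untreated arm, so that effect cannot be separated from retest, habituation or natural course. The Discussion sentence on sensory gating does not mention this.

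**Working it through.** **Inputs from the document.** 30 participants in total (Study design) and 15 in the experimental group (Procedure), so 15 per arm; two visits; no power calculation (Sample size). The document gives no EEG standard deviation, effect size or pre/post correlation, so there is no planned figure to reproduce.

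**Assumptions.** Pre/post correlation r between 0.3 and 0.7, with 0.9 as a limiting case; equal SD at both visits; all 30 participants with both recordings. Results are in units of that SD.

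**Step 1: what the planned model estimates.** With two visits and two arms, the group-by-time F test of a repeated-measures ANOVA is identical to a two-sample t-test on (post − pre).

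**Step 2: variances.** In units of SD² × 2/n, for n per arm:
- change score: 2(1 − r)
- ANCOVA, large sample: 1 − r²
- ratio ANCOVA/change: (1 − r²) / [2(1 − r)] = (1 + r)/2

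Estimating the baseline slope costs an approximate factor 1 + 1/(2n − 4). With n = 15 this is 1 + 1/26 = 1.038.

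**Step 3: 95% CI half-widths.**
- change score: t(0.975, 28 df) × √[2(1 − r)] × √(2/15)
- ANCOVA: t(0.975, 27 df) × √(1 − r²) × √(2/15 × 1.038)

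| r | (1 + r)/2 | ratio with small-sample factor | half-width, change score | half-width, ANCOVA |
|---|---|---|---|---|
| 0.3 | 0.65 | 0.68 | 0.89 | 0.73 |
| 0.5 | 0.75 | 0.78 | 0.75 | 0.66 |
| 0.7 | 0.85 | 0.88 | 0.58 | 0.55 |
| 0.9 | 0.95 | 0.99 | 0.33 | 0.33 |

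The variance advantage ends where (1 + r)/2 × 27/26 = 1, that is at r = 52/27 − 1 ≈ 0.93.

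**Step 4: attrition.** With 12 per arm (80% of 15), the half-widths are 1.00 against 0.83 at r = 0.3, 0.85 against 0.75 at r = 0.5, and 0.66 against 0.62 at r = 0.7. The pattern is the same.

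**Step 5: simulation.** 20,000 trials per setting, 15 per arm, no arm difference, and an assumed drift of 0.3 or 0.5 SD common to both arms.
- *Precision.* At a drift of 0.3 SD, the SD of the between-arm estimate was 0.434 (change score) and 0.353 (ANCOVA) at r = 0.3, 0.366 and 0.322 at r = 0.5, and 0.284 and 0.265 at r = 0.7. The squared ratios are 0.66, 0.77 and 0.87, close to the table.
- *Type I error of the between-arm test.* About 5% for both methods in every setting.
- *Time main effect.* Significant at 5% in 27% to 61% of trials at r = 0.3, 36% to 75% at r = 0.5, and 54% to 93% at r = 0.7, the lower figure for the smaller drift. The test is correctly detecting a change over time. It carries no information on whether the therapy caused that change.

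**The case against.** The strongest reply is that nothing here is invalid. The group-by-time term is an unbiased randomised comparison with correct type I error. The ANCOVA sentence covers clinical outcomes, so a different model for EEG is not a contradiction. Repeated-measures ANOVA also matches the two-part P50 hypothesis, with time for the first half and group-by-time for the second. EEG is exploratory, the sample size is not power-based, and the feasibility and acceptability outcomes are untouched. All of this stands. It limits the point to efficiency and wording but does not remove the gain in precision.

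A reader might be tempted by four stronger readings that the document does not support:
- *That the EEG analysis ignores the randomised arms.* The methods sentence names no group term, but the hypothesis and the Discussion both show that a between-arm comparison is intended. Model terms may sit in a fuller plan that is not shown.
- *That the article claims a causal effect of therapy on P50.* The Discussion sentence is conditional and hedged, and the same section says the exploratory measures are not there for confirmatory testing.
- *That ANCOVA would cure the uncontrolled time effect.* It would not. No model supplies an untreated arm, so this is a separate and smaller point.
- *That P50 is left undefined because S1, S2 and their ratio are all extracted, or that EEG has no missing-data rule.* An article may leave both to the full plan.

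The size of the gain also rests on a correlation that the document does not give.

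**Conclusion.** The point holds as a recommendation on efficiency, with a minor point on interpretation. The planned EEG model is valid but gives a wider interval for the between-arm contrast than the method the article already uses for clinical outcomes. Under the assumed r of 0.3 to 0.7, with 15 per arm and equal SDs at both visits, ANCOVA reduces the variance by about 32% to 12%. The gain is negligible near r = 0.9 and absent above about 0.93. Separately, the change over time common to both arms is uncontrolled and cannot support a statement about the effect of VR therapy on sensory gating. Neither point affects the trial's feasibility conclusions.

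**What to change.** 1. In the Analysis of EEG data section, state that the between-arm contrast for P50 and the other EEG measures is estimated by ANCOVA: the 12-week value on arm and the corresponding EEG baseline value, reported as a difference with its 95% CI. Make the change before EEG data are compared by arm, so that the choice of model does not follow the results.
2. Report pooled and within-arm pre/post change, which addresses the first half of the P50 hypothesis, as uncontrolled description.
3. Qualify the Discussion sentence on sensory gating: say that without an untreated arm a post-treatment improvement cannot be attributed to the intervention, and that only the between-arm difference bears on the added effect of biofeedback.

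The cost is one residual degree of freedom (27 instead of 28 at full sample), a few sentences of text, and giving up any formal causal reading of the time effect. No new data, visits or participants are needed.
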